### Randomization

2.4

Patients who meet the criteria will be randomly allocated to the lidocaine group or to the control group. Randomization will be computer generated with allocation ratio 1:1. Randomization and enrollment will be done by an independent physician who is not directly involved in the care of the patients. Anesthesiologist will not be blinded to the grouping, but the participants. Unblinding could be done in case of any medical emergency. In case of unblinding, the patient will be excluded from the trial. Allocation concealment will be ensured with closed envelop method, which cannot be opened until induction of the anesthesia have been completed

### Interventions

2.5

Patients included in the trial will be randomly assigned to the lidocaine group (Group L) or to the control group (Group C). Patients in Group L, following general anesthesia induction, will receive topical anesthesia of the throat before endotracheal intubation with 40 mg of lidocaine and also regional anesthesia of the scalp with 2% lidocaine in maximum dosage 4 mg/kg before Mayfield frame placement. Total dosage of lidocaine will be up to 400 mg. Regional anesthesia of the scalp will be performed using technique described in relevant literature.^[16]^ Patients in Group C will have general anesthesia only without any lidocaine administration. All patients will undergo craniotomy and cerebral aneurysm clipping surgery with preoperative placement of lumbar CSF drainage, when it is otherwise indicated neurosurgically.

Blood samples will be taken from every patient included in the study at four timepoints: before induction of the anesthesia (baseline), at the time of incision, at the end of surgery and 24 hours from start of anesthesia. CSF samples will be taken from lumbar CSF drainage system at 2 timepoints: at the time of incision and at the end of surgery. Concentrations of IL-1β, IL-6, and TNF-α in plasma and CSF will be measured using enzyme-linked immunosorbent assay (ELISA) specific for each cytokine, according to manufacturer instructions.

### Anesthesia management

2.6

During the surgical procedure, the following standard monitoring will be used: electrocardiography (ECG), pulse oximetry (SpO2), invasive and noninvasive blood pressure measurements, end-tidal carbon dioxide (ETCO2), entropy, body temperature, and urine output. Induction of general anesthesia will be performed with fentanyl, propofol and rocuronium. After tracheal intubation, mechanical ventilation will be commenced to maintain normoxia and normocapnia with tidal volume of 8 to 10 ml/kg, respiratory rate of 10 to 14 per minute, fraction of inspired oxygen of 50% and fresh gas flow rate of 3 liter per minute. Anesthesia will be induced and maintained with continuous intravenous infusions of propofol 100 to 200 mcg/kg/minute and fentanyl 1 to 2 mcg/kg/hour, adjusted to entropy monitoring. No inhalation anesthetic agent will be used. Fluid balance will be closely monitored and crystalloid infusions will be used for fluid therapy. Arterial blood pressure will be continuously monitored and recorded. Vasoactive agents will be used to maintain target values of mean arterial pressure (±30% of baseline values), depending on clinical scenario, with phenylephrine 0,5 mcg/kg/minute or noradrenaline 0,01 mcg/kg/minute. Dosages of anesthetic drugs used will be recorded as well as all the monitored clinical parameters. At the end of the surgery, patient will be transferred to the intensive care unit where the patient will be safely extubated. Time of extubation will also be recorded.

Monitoring of ECG, SpO2, ETCO2, and arterial blood pressure will be continued in intensive care unit. After extubation, GCS will be recorded at every hour for the first 48 hours after surgery. Patients will be monitored for neurological and infectious complications during hospital stay and their incidence will be recorded. Any new focal motor deficit or fall in GCS by 2 points or more will be considered significant, as well as any seizure occurrence. Development of significant vasospasm will be diagnosed by clinical signs and confirmed by transcranial Doppler ultrasound (blood flow velocity more than 180 cm/seconds over middle cerebral artery). Any major pathology found on postoperative brain computerized tomography (CT) will also be recorded (bleeding, ischemia, edema, or hydrocephalus). The study will monitor for any potential intervention-related adverse events daily through patient examination and chart review. All data will be entered electronically and coded to maintain participant confidentiality. This will be done at the Center where the data originated. Original forms will be stored securely for a period of 3 years after completion of the study. All investigators will be given access to the final data sets and we will deliver a completely deidentified data set to an appropriate data archive for sharing purposes.

### Primary outcome

2.7

The primary outcome are concentrations of IL-1β, IL-6, and TNF-α in plasma and CSF of patients undergoing craniotomy for cerebral aneurysm surgery under general anesthesia. These cytokines will be measured at specific timepoints, as described.

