## Statistical analysis plan

3

The analysis will be conducted by Statistical Package for the Social Sciences (SPSS) Statistics software, version 25.0 (IBM Corporation, Armonk, NY). Continuous and ordinal data will be presented as the median and interquartile range (IQR), while categorical data will be presented as raw numbers and as frequencies. Distribution of data will be tested by the Kolmogorov-Smirnov and Shapiro-Wilk tests. Non-parametric tests like Friedman's 2-way ANOVA with post-hoc Dunn test and Mann–Whitney *U* test will be used to assess pair-wise differences between related and independent variables with non-normal distribution. Data with normal distribution will be analyzed by Student *t* test. Correlations will be analyzed with Spearman test. For sensitivity-specificity measurements, the receiver operator characteristics (ROC) curve estimation will be used. Values of *P* < .05 is considered significant. An interim-analysis is performed on the primary endpoint when 50% of patients have been randomized. The interim-analysis is performed by an independent statistician, blinded for the treatment allocation.

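### Fifteen post-lidocaine cytokine results share primary status at an undivided P < .05, with no lead comparison and no rule for which results confirm the hypothesis

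*Protocol article*

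**What the plan says.** Section 2.7 of the protocol article defines the outcome: "The primary outcome are concentrations of IL-1β, IL-6, and TNF-α in plasma and CSF". It adds "These cytokines will be measured at specific timepoints, as described", so no cytokine, fluid or time is set above the others.

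Section 2.5 gives the schedule. Blood is drawn "at four timepoints: before induction of the anesthesia (baseline), at the time of incision, at the end of surgery and 24 hours" after the start of anaesthesia. For the other fluid, "CSF samples will be taken from lumbar CSF drainage system at 2 timepoints: at the time of incision and at the end of surgery". Lidocaine comes after the first blood sample: "Patients in Group L, following general anesthesia induction, will receive topical anesthesia of the throat before endotracheal intubation".

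Section 3 sets a single threshold: "Values of *P* < .05 is considered significant". It lists Friedman's test with Dunn's post-hoc test, the Mann–Whitney test and the t test. It also plans an interim analysis of the primary endpoint, in the singular, at 50% randomised.

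Section 2.9 uses α = 0.05 and β = 0.1 and arrives at a minimum of 20 per group for pair-wise comparisons. It states no effect size or standard deviation. The introduction and discussion put the hypothesis jointly: lidocaine lowers all three cytokines in both fluids.

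**The concern.** A 5% error rate and 90% power describe one comparison. Here they are attached to a family of results that all carry the label primary, and the article does not say how the family is to be read.

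The only multiple-comparison step named, Dunn's test after Friedman, deals with repeated timepoints within a group. It does not protect the comparison of Group L with Group C across cytokines, fluids and times.

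What is at stake is the meaning of a positive trial. Without a named comparison or a success rule, the result to emphasise could be chosen after the P values are known. The interim statistician also has no single endpoint to analyse.

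**Working it through.** **1. Counting the results** (sections 2.5 and 2.7)
- Plasma: 3 cytokines × 4 times = 12. CSF: 3 × 2 = 6. Total 18.
- The three plasma baseline values precede induction, and so precede lidocaine. They cannot show an effect: 18 − 3 = 15.

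**2. The plan's own figure** (section 2.9)
- The 20 per group cannot be reproduced, because no difference or SD is given. Solving backwards for a two-sided α of 0.05 and 90% power: d = (1.960 + 1.282) × √(2/20) = 1.03 SD. With the t distribution it is 1.05 SD.
- This is the difference for one comparison at an undivided 0.05.

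**3. If any one significant result counts**

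Assumptions: one two-sided between-group test at 0.05 per post-lidocaine result, and no true effect. The documents give no correlations and do not state sidedness.
- Independent results: 1 − 0.95^15 = 0.537.
- False decreases only, independent: 1 − 0.975^15 = 0.316.
- Equally correlated normal test statistics, by simulation:

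| Assumed correlation | Any false positive | False decrease only |
|---|---|---|
| 0 | 54% | 32% |
| 0.3 | 46% | 23% |
| 0.5 | 36% | 18% |
| 0.8 | 20% | 10% |

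- Simulated Mann–Whitney tests at 20 per group agree. With assumed correlations of 0.3 between cytokines, 0.3 between fluids and 0.5 between adjacent times, the chance of any false positive is 48%. With 0.8, 0.8 and 0.9 it is 24%.
- None of these figures includes the interim look.

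**4. If every result must be significant**
- The error stays at or below 5%, but joint power falls. At 90% per test and independence it is 0.9^15 = 21% for 15 tests and 0.9^6 = 53% for six.
- Correlation raises these figures. Simulating 15 normal test statistics with mean 1.960 + 1.282 = 3.24 and equal correlation 0.8, all 15 exceed 1.96 in about 71% of runs, still short of 90%.

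**5. If six tests stay primary** (one per cytokine and fluid)
- Holm's smallest threshold is 0.05/6 = 0.0083.
- Power for that test at 1.05 SD and 20 per arm is 70%. A power of 90% would need 30 per arm.
- CSF comes only from patients with an indicated lumbar drain (section 2.5). At an assumed 15 per arm, power for that test is about 53%.

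**The case against.** Much of the case on the other side is sound, and it limits what can be claimed.

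- A reader might infer that a false positive is likely, meaning more likely than not. Among the 15 results that holds only close to independence. Related cytokines measured repeatedly in the same patients will be correlated, and every moderately correlated scenario above falls below one half.
- A reader might count 18 chances of a false claim (1 − 0.95^18 = 60% if independent). Three of these are pre-treatment values, and a difference there would not be read as a lidocaine effect.
- The hypothesis is a decrease. With two-sided tests, false increases would not support it, which roughly halves the figures. If the tests are one-sided at 0.05, this reduction does not apply.
- A reader might infer that one significant result is enough. The article never says so, and its joint hypothesis could mean that all must be significant. That reading protects the error rate but gives up the stated power.
- A condensed article may leave adjustment methods to a fuller plan. That is fair for the detail. But the article itself gives every result primary status and sets the flat threshold, under its own analysis-plan heading. Those two statements are what need repair.
- The trial is small and its claims are modest. Even so, it is framed as testing a hypothesis and is sized at 90% power, so a success criterion is needed.

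**Conclusion.** The point holds in a limited form. The defect is that no primary comparison and no success rule are identified, although the sample size and the interim analysis both presuppose one.

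On the any-one reading, error lies between about 20% and 54%, roughly 4 to 11 times nominal. Counting decreases only, it is about 10% to 32%, or 2 to 6 times nominal. These ranges rest on one two-sided test per post-lidocaine result and on assumed equal correlations from 0.8 down to 0. On the all-results reading there is no inflation, but 90% power is not available across the correlations examined. The documents do not choose between these readings, so neither can be presented as the plan's rule.

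It should be settled before results are compared by group, because a choice made afterwards cannot be shown to be independent of the data.

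**What to change.** By formal amendment (the route in section 2.12), and before any group comparison, including the interim, is seen:

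1. **Preferred.** In section 2.7, name one cytokine, one fluid and one timepoint, Group L versus Group C, as the primary comparison. Make all other results secondary, reported with confidence intervals. Plasma is the better-supported fluid because every patient is sampled. The cytokine is the sponsor's choice: the introduction links both IL-6 and TNF-α to complications and gives IL-1β the microglial rationale. Use the same comparison for the interim analysis.
2. **If all three cytokines in both fluids stay primary.** Fix one timepoint or summary measure per cytokine and fluid, apply Holm to the six tests at an overall 5%, and restate the power, allowing for the number of patients expected to have a drain.

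In either case, state in section 2.9 the difference and SD behind the 20 per group.

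The first option costs protocol and registry wording and a narrower primary claim; the nominal 5% and the 20 per group then apply to the named comparison. The second keeps the broader claim but lowers the stated power, to about 70% for the smallest-alpha test at 20 per arm and 1.05 SD, and lower for CSF. If a group comparison has already been seen, the amendment should say so and the choice should be reported as made afterwards.

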### Secondary outcomes

2.8

1.Incidence of neurological complications within the first 7 postoperative days: new focal motor deficit, decrease of GCS by 2 points or more, seizure, signs of vasospasm, pathological finding in brain CT scan.2.Incidence of infectious complications within the first 7 postoperative days: meningitis, pneumonia, or sepsis.3.Outcome assessment will be done by using Glasgow outcome scale at the end of hospital treatment.

### Sample size calculation

2.9

Based on previous studies, we performed a sample size estimation before recruitment with the power analysis module of STATISTICA software version 10.0 (StatSoft Inc., San Diego, CA), using α = 0.05 and β = 0.1.^[17,18]^ We determined that a minimum of 20 participants was required per group for pair-wise comparisons of our samples.

### Timeline

2.10

This is an 18-month study, which started in March 2019 and will be ended in September 2020.

### Safety

2.11

The incidence of side effects during entire postoperative period will be closely monitored and recorded, as well as adverse events and complications. In case of any adverse events or complications, the administration of lidocaine will be immediately stopped in Group L and patient will be excluded from further interventions of this study.

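### The only period named for side-effect collection is after surgery, but all lidocaine is given before the head frame is placed, and the stop-lidocaine clause has nothing left to act on by then

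*Protocol article*

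**What the plan says.** Section 2.5 gives Group L lidocaine twice, both times after induction. The first dose goes to the throat before intubation. The second is "regional anesthesia of the scalp with 2% lidocaine in maximum dosage 4 mg/kg before Mayfield frame placement". No later lidocaine is described, and Group C receives none.

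Section 2.11 says on collection: "The incidence of side effects during entire postoperative period will be closely monitored and recorded". The same sentence goes on to add adverse events and complications. It then says on action: "In case of any adverse events or complications, the administration of lidocaine will be immediately stopped in Group L", and adds that the "patient will be excluded from further interventions of this study".

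Section 2.6 bears on this in two places. For the operation it lists ECG, oximetry, blood pressure and other standard monitoring, and adds: "Dosages of anesthetic drugs used will be recorded as well as all the monitored clinical parameters". In the paragraph on intensive care and the hospital stay it says: "The study will monitor for any potential intervention-related adverse events daily through patient examination and chart review".

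**The concern.** A drug given only before incision is most likely to show acute side effects during dosing and the operation that follows. The Introduction itself describes lidocaine as an antiarrhythmic with significant systemic effects. The patient is anesthetised in those hours and cannot report symptoms, so any signal has to come from the monitors. The Safety section ties side effects to the time after surgery, and no sentence turns the intraoperative recordings into adverse events.

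Two things are at stake. First, a rhythm or pressure disturbance soon after dosing could sit in the anesthesia record and never reach the side-effect count. Second, the clause that stops lidocaine cannot be carried out for an event first seen after surgery. The other half of that sentence, on further interventions, then becomes the only operative part, and its meaning for the remaining samples is unclear. Those samples supply the primary outcome.

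**Working it through.** The documents give no safety figure to reproduce. The check is one of timing, plus some counting.

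**1. Order of events** (sections 2.5 and 2.11): induction, throat lidocaine, intubation, scalp block, frame placement, incision, end of surgery, postoperative period. The last lidocaine precedes the named side-effect period by the whole operation.

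**2. Length of the gap.** Gap = (throat dose to start of surgery) + (duration of surgery). The first term is not given. The second is at most 6 hours in analysed patients, because section 2.3 removes longer operations from the analysis. This assumes that surgery time excludes the preparation before incision, which the article does not define.

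**3. What is captured in the gap.** Section 2.6 records the monitored parameters. The outcomes in sections 2.7 and 2.8 are cytokine concentrations, neurological and infectious complications in the first 7 postoperative days, and the Glasgow outcome scale at the end of hospital treatment. None of these uses intraoperative rhythm or pressure, and section 2.11 does not refer to them either.

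**4. Reach of the stop clause.** Section 2.5 schedules blood at baseline, incision, end of surgery and 24 hours from the start of anesthesia. It schedules CSF at incision and end of surgery, in patients with a lumbar drain.

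| When the event is seen | Lidocaine left to stop | Blood samples left | CSF samples left |
|---|---|---|---|
| Throat dose to end of scalp block | Remainder of the scalp block | 3 | 2 |
| End of scalp block to incision | None | 3 | 2 |
| After incision, before end of surgery | None | 2 | 1 |
| After surgery, before the 24-hour sample | None | 1 | 0 |

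The clause has an object only in the first row. In the other three rows, only the exclusion from further interventions can apply. The sampling schedule stands in the section headed Interventions, so a reader cannot tell whether the samples in the last two columns are still to be drawn.

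**5. Scale.** With the planned minimum of 20 per group (section 2.9), one uncounted event changes an arm's rate by 1/20 = 5 percentage points. Even a complete count of 0 in 20 has a one-sided 95% upper limit of 1 − 0.05^(1/20) = 0.139, or 13.9%. Safety tables from this trial can describe but not exclude. How many events would be missed cannot be derived from the documents.

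**The case against.** The strongest reply is that the collection sentence does not end with side effects. It goes on to adverse events and complications, and those words are not clearly tied to the time after surgery. The stop clause is triggered by adverse events or complications, not by side effects, so it may assume detection while lidocaine is being given. It has some scope then, because there are two administrations. Intraoperative parameters are recorded, and the chart review in section 2.6 is not limited to postoperative entries, so it could pick up an event from the anesthesia record. Finally, a journal article commonly leaves adverse-event definitions and reporting forms to the full protocol, and tabulations of pressure or vasoactive use would be an addition.

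Most of this stands, and it limits the point. It does not remove it. The article does not merely omit a window for side effects: it states one, and that window begins after the exposure. That chart review may reach back into the operation is a possibility, not an instruction. The stop clause is likewise stated, and for a postoperative event it does not fit section 2.5.

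A reader might infer more than the documents support:

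- That the exposure hours are unobserved. They are not, since section 2.6 monitors and records them.
- That stopping lidocaine is the only safety action. It is not, since the same sentence also excludes the patient from further interventions.
- That the safety comparison has no control rate, because section 2.6 speaks of events related to the intervention. The phrase there is any potential such event, section 2.11 records adverse events and complications without limiting them to an arm, and the complications in section 2.8 are defined without reference to attribution. Only the stopping of lidocaine is specific to Group L.

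**Conclusion.** The point holds in a limited form. The stated side-effect period begins after all lidocaine has been given and after the operation, and nothing says that the intraoperative recordings are assessed as adverse events. Side effects near dosing may therefore go uncounted. The documents do not show that they will, and they give no basis for estimating how many.

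Separately, the stop-lidocaine clause can act only between the throat dose and the end of the scalp block. Sections 2.5 and 2.11 must be reconciled, including what exclusion from further interventions means for samples not yet drawn.

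This rests on two assumptions: that no lidocaine is given beyond the two administrations described, and that the full protocol does not already open collection at induction. The analysis of the cytokine outcomes is touched only through the unclear exclusion wording. This is an inexpensive improvement to the safety reporting, not a threat to the main comparison. No clinical rule is proposed here.

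**What to change.** Make three changes of wording:

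1. State in section 2.11 that adverse events are collected from induction onward in both groups, whatever their presumed cause. Under section 2.4 the allocation envelope stays closed until induction is complete, so this start is the same for both groups and does not depend on allocation.
2. State that rhythm events, arterial pressure events and vasoactive use during surgery will be tabulated by arm as descriptive safety data, from the records kept under section 2.6. Define each event before the data are viewed by arm. Intubation and frame placement occur in both groups and can anchor the timing.
3. Reconcile the stop-lidocaine sentence in section 2.11 with the two administrations in section 2.5, and say whether a patient excluded from further interventions still gives the remaining blood and CSF samples. The investigators must decide the content.

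The cost is an amendment and a few form lines. ECG and arterial pressure are already recorded, and patients already treated can be abstracted from the existing records. Section 2.6 does not name vasoactive agents in its recording sentence, so one form line may be needed for them. No extra procedure or patient is required. The small downside is that more events will be listed in both arms.
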